**SUPPORTING INFORMATION: Trial Protocol**

# Effects of rhGH and Pioglitazone in Viscerally Obese Adults with IGT

A. **ABSTRACT**

People with impaired glucose tolerance (IGT) who lose visceral fat also tend to lower their risk of developing diabetes. This benefit occurs because visceral fat reduction improves insulin sensitivity and reduces postprandial glucose levels. Thiazolidinediones (TZDs) and growth hormone (rhGH) taken independently foran *extended period of time* can reduce visceral fat and improve endogenous insulin sensitivity. However, in the *short-term* (ie: first 6 weeks of treatment) rhGH may increase insulin resistance. In contrast, a TZD added to rhGH prevents short-term rhGH-induced insulin resistance in experimental animals, suggesting a possible therapeutic benefit with this drug combination in humans. In addition, like rhGH, TZDs mediate some of their insulin sensitizing effects by reducing visceral fat depots. It is therefore possible that the addition of a TZD with standard growth hormone therapy will optimize the short-term and long-term improvements in body composition, insulin sensitivity and glucose metabolism in humans.

The specific aims of this study are as follows: (1) to assess the effects of TZDs with and withoutrhGH on visceral fat content, insulin sensitivity and postprandial glucose levels in viscerally obese subjects with IGT; *and* (2)to compare the effects of TZDs *plus* rhGH with rhGH alone on short-term glucose metabolism. Sixty adult men and women between the ages of 40 and 75 will be recruited to participate and will receive a TZD and rhGH in a double-blind manner. During weeks 0-4, a “run-in” period, subjects will receive a TZD or oral placebo. During weeks 5-40, a TZD or oral placebo will be co-administered with rhGH or a subcutaneous placebo in a 2 X 2 study design. Short-term glucose metabolism will be monitored using fasting glucose levels. Changes in visceral fat content will be quantified using abdominal CT scanning and anthropometric measurements. At baseline and after 9 months of combination drug or placebo treatment, serum postprandial glucose levels will be measured using a standard oral glucose tolerance test, and endogenous insulin sensitivity will be measured using a hyperinsulinemic euglycemic clamp.

It is expected that the combined use of a TZD and rhGH will be more efficacious in reducing visceral fat quantity and improving insulin sensitivity in viscerally obese adults with IGT compared with the use of either drug alone. The potential long-term benefit of this finding is a reduction in the incidence of type 2 diabetes in populations at high risk of developing diabetes, such as individuals with visceral obesity and IGT.

B. **HYPOTHESES AND SPECIFIC AIMS TO TEST HYPOTHESES**

***Hypothesis #1:*** Subjects who receive rhGH and pioglitazone for 9 months will achieve greater visceral fat reduction, improved insulin sensitivity and lower postprandial glucose levels compared with subjects who receive placebo.

***Specific aim to test hypothesis #1:*** We will assess the effects pioglitazone with and without prolonged rhGH administration on visceral fat change and determine whether change in visceral fat quantity is associated with changes in endogenous insulin sensitivity and postprandial serum glucose levels.

***Hypothesis #2:***Subjects who receive pioglitazone *and* rhGH will demonstrate less transient worsening in glycemic control during the first 6 weeks of treatment compared with subjects who receive rhGH alone.

***Specific aim to test hypothesis #2:***We will compare the effects of a TZD *plus* rhGH with rhGH alone on short-term glucose metabolism. In doing so, we will also determine whether the co-administration of a TZD can effectively counteract the expected transient rise in insulin resistance associated with rhGH and help to maintain better short-term postprandial glucose control compared with rhGH alone.

C. **BACKGROUND**

***Link between visceral fat and cardiovascular disease:***   In recent years, we have gained a better understanding of the relationship between cardiovascular (CV) disease and various components of body fat such as total body, subcutaneous and intra-abdominal (or visceral) fat. Several epidemiological studies have indicated that, of these components, visceral fat – a combination of omental and mesenteric adipose tissue – is the greatest predictor of CV disease and events. Rexrode et. al prospectively followed 45,000 older women over 8 years to determine the effect of visceral fat on CV outcome. Women with android obesity – that is, a large waist circumference (ie: >98.5 cm) and a large waist-to-hip ratio (ie: > 0.88) – had a more than twofold increased risk of coronary heart disease even after adjustment for hypertension, diabetes and high cholesterol levels, and even when body mass index (BMI) was normal (1).

Conversely, several prospective studies have indicated that a selective reduction in visceral fat reduces CV disease risk by improving hypertension, dyslipidemia, diabetes and other components of intermediary metabolism (2-7).

***Link between visceral fat and impaired glucose tolerance:*** Normal glucose homeostasis is maintained by a combination of sufficient insulin release from pancreatic islet cells and adequate tissue sensitivity to insulin. Insulin sensitivity is often diminished with visceral obesity, and when the pancreas fails to release enough insulin to overcome this resistance to insulin, a condition known as impaired glucose tolerance, or IGT, develops.

IGT is a pre-diabetic condition that is very common in viscerally obese adults and is defined by abnormally high postprandial glucose levels after a 75-gm oral glucose load (8). It is associated with adverse health consequences, including an increased risk of developing type 2 diabetes and an increased risk of cardiovascular disease (9-11). The exact cause of the increased CV risk in adults with IGT is unknown, but the postprandial hyperglycemia itself may be responsible.  Postprandial hyperglycemia appears to generate oxidative stress, increase protein glycation, increase hypercoagulability, and damage endothelial cells ­- all of which lead to atherosclerosis (12).

Visceral fat loss reduces postprandial glucose levels in IGT patients (13-19). Fujioka et. al showed that weight loss - and visceral fat reduction in particular - results in a significant reduction in postprandial glucose levels in viscerally obese women with IGT (20). Eriksson et. al also prospectively showed that IGT subjects achieved lower postprandial glucose levels after weight loss, and that this reduced the overall risk of developing type 2 diabetes (21). In addition, recently published data from the Diabetes Prevention Program (DPP) study indicate that a 5-7 % weight loss in IGT subjects reduces the risk of developing type 2 diabetes by 58% (22).

***GH, visceral fat reduction and enhanced insulin sensitivity:*** Growth hormone (GH), a glycopeptide hormone produced in the anterior pituitary, helps to maintain normal body composition and reduce visceral fat in adults (23). It also appears to have various effects on glucose, lipid and bone metabolism.

Viscerally obese adults have below normal integrated GH concentrations as measured by an ultrasensitive chemiluminescence assay (24). The association between visceral obesity and an apparent “underproduction” of GH has recently prompted several investigators to study the effects of rhGH on body composition and metabolism in viscerally obese adults. In a recent study, Johannsson et. al investigated the effects of rhGH in insulin resistant, viscerally obese men with normal glucose tolerance (25). As expected, subjects receiving rhGH lost a substantial amount of visceral fat – almost 18%. In addition, while overall glucose levels did not change during the study, an interesting paradoxical effect on short-term versus long-term insulin sensitivity occurred in rhGH-treated subjects. RhGH-treated subjects developed a transient *decrease* in insulin sensitivity as expected during the first 6 weeks of therapy. However, after 9 months of rhGH treatment, the glucose disposal rate (GDR), a measure of tissue insulin sensitivity*, increased* by 1.2 +/- 0.7 mg/kg per minute compared to baseline (*P* < 0.05), indicating that insulin sensitivity increases – rather than decreases - with long-term rhGH administration.

    How does GH cause a *transient* insulin resistance? GH exerts a direct antagonistic effect on the insulin signaling pathway in muscle cells. GH inhibits the insulin-induced activation of so-called insulin receptor substrate (IRS) proteins, and these “inactivated” proteins cannot trigger the usual cascade of events that ultimately lead to glucose uptake into tissues. Despite the antagonistic effects of GH on insulin, euglycemia is usually maintained because the pancreatic beta-cell increases insulin output in order to overcome tissue insulin resistance.

    What causes the subsequent increase in insulin sensitivity that occurs with prolonged rhGH administration? Visceral fat loss. This happens as follows: visceral fat, a vast depot of lipid-rich substances, releases large quantities of free fatty acids (or FFAs) into the circulation. FFAs cause insulin resistance by blocking the insulin-induced expression and cell surface translocation of proteins that mediate glucose transport into cells, called glucose transporter (or GLUT) proteins. A selective reduction in visceral fat, as occurs with prolonged rhGH administration, leads to diminished free fatty acid (FFA) flux, and this allows insulin-GLUT-mediated glucose disposal to occur. While rhGH directly antagonizes insulin in skeletal muscle, rhGH-induced visceral fat disappearance leads to enhanced insulin action in *multiple* tissue compartments, including adipocytes, skeletal tissue, hepatocytes, and other cells throughout the body. As a result, the indirect insulin “sensitizing” effects of visceral fat reduction with prolonged rhGH administration outweigh its direct insulin resistant effects, and the net result is a rise in endogenous insulin sensitivity (25).

    Visceral fat reduction and the insulin sensitive state that follows help to lower postprandial glucose levels in individuals with IGT. Postprandial glucose reduction occurs in this setting because insulin, now free from the antagonizing effects of FFAs, is able to turn off gluconeogenesis, or glucose production, in the liver and stimulate the uptake and clearance of glucose into muscle and other tissues. It is possible that similar improvements in glucose metabolism will occur in viscerally obese IGT patients who receive rhGH. However, this is theoretical. Prospective studies are needed to determine the effects of prolonged rhGH on glucose metabolism in this population.

***Thiazolidinediones plus rhGH: effects on glucose metabolism:*** Like rhGH, insulin sensitizer drugs known as thiazolidinediones help to improve endogenous insulin sensitivity – albeit by a somewhat different mechanism than rhGH. *Prolonged* rhGH improves insulin sensitivity primarily by reducing visceral fat content, which reduces free fatty acid flux in the circulation, thus removing a potent barrier to normal insulin signaling. TZDs are synthetic ligands that activate the nuclear receptor known as peroxisome proliferator activated receptor gamma, or PPAR gamma. The activation of PPAR gamma modulates the expression of various genes in the insulin signaling pathway. This, in turn, facilitates insulin’s action at the cellular level and allows glucose uptake to occur. The in vitro and in vivo insulin sensitizing effects of TZDs in adipocytes have been well characterized in animal models and are correlated with both PPAR gamma activation and increased expression of glucose transporter (or GLUT) proteins (26,27,28).

TZDs have been shown to completely overcome the *transient* insulin antagonizing effects of rhGH in animals (29). According to Sugimoto et. al 1998, rats treated with rhGH and a TZD maintained normal glucose homeostasis and insulin sensitivity during the period in which this drug combination was used, whereas rats treated with rhGH alone developed insulin resistance and abnormal glucose control (including impaired glucose tolerance). This study also demonstrated that the co-administration of a TZD (troglitazone) with rhGH helped to overcome the antagonizing effects of rhGH on insulin- mediated peripheral tissue glucose utilization and helped to restore insulin’s ability to suppress hepatic glucose production.

TZDs therefore may improve endogenous insulin sensitivity via several mechanisms, including PPAR gamma activation and increased expression of GLUT proteins in adipocytes and perhaps skeletal muscle and other tissues. In addition, a TZD called pioglitazone appears to improve insulin sensitivity by at least one additional very interesting mechanism: shifting or redistributing body fat from visceral fat depots to subcutaneous fat depots. Miyazaki and colleagues noted this finding in a recent study involving the treatment of insulin-resistant type 2 diabetics with pioglitazone (29a). In this study, 16 weeks of treatment with pioglitazone resulted in a reduction in visceral fat area of 9 % at L 4-5 compared to baseline (P <0.05) and a decline in the visceral fat: subcutaneous fat ratio of 25% at L 4-5 compared to baseline (P <0.01) (29a). The shift in fat content from the viscera to the periphery after 16 weeks of pioglitazone treatment was also associated with a statistically significant increase in hepatic insulin sensitivity in the postabsorptive state and higher total body glucose disposal rates as measured by the insulin clamp technique.

In summary, either rhGH or a TZD taken for a prolonged period can reduce visceral fat and improve endogenous insulin sensitivity. However, no human trials to date have prospectively assessed the combined effects of rhGH and a TZD over an extended period on visceral fat change, insulin sensitivity, and glucose homeostasis. It is anticipated that the combination of a TZD and rhGH will have an additive or synergistic effect in improving body composition and glucose homeostasis compared with either drug alone. This in turn would be very efficacious in delaying or preventing type 2 diabetes in viscerally obese adults IGT. It is also anticipated that TZDs will counteract the *transient* insulin antagonizing effects of rhGH and therefore allow this potent drug combination to be used to achieve its long-term benefits.

This protocol would be the first to test the hypothesis that viscerally obese IGT subjects who receive pioglitazone *and* rhGH will demonstrate at least 2 very important benefits: (a) in the short-term, less *transient* worsening in glycemic control compared with subjects who receive rhGH alone; and (b) in the long-term, a greater *reduction* in visceral fat quantity, insulin resistance and postprandial glucose levels compared with placebo or rhGH given alone.

D. **RESEARCH PLANS**

**Subjects:** Men and women between the ages of 40 and 75 with visceral obesity and IGT will be recruited to participate. This age group has a higher prevalence of both visceral obesity and IGT.

Specific inclusion criteria are as follows: (a) adults between the ages of 40 and 75; (b) fasting glucose less than 120 mg/dl PLUS 2 hour postprandial glucose level during 75 gram OGTT between 140 – 200 mg/dl; (c) BMI > 27; and (d) increased waist circumference and/or increased waist-to-hip ratio (*see anthropometric measurements* below).

Subjects will be free of major medical illnesses such as uncontrolled hypertension, congestive heart failure or active malignancies. Women of child-bearing potential who are or plan to become pregnant or will breastfeed an infant will be excluded. Subjects taking corticosteroids or other medications that can significantly alter glucose metabolism will also be excluded. Groups will be matched on gender, BMI, estrogen status, and 2-hr glucose level (during screening OGTT). A third party investigator will be responsible for all randomization and coding of medications and placebo.

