#### STUDY ENDPOINTS

**Oral glucose tolerance test:** As per the technique described under screening, a 75 gram OGTT will be repeated at week 43, approximately 3 weeks after discontinuation of all study medications (washout period). In addition, the glucose area under the curve, or AUC, will be measured using the trapezoid method. Based on previously published data, we expect that rhGH administration will cause at least a 10% reduction in both postprandial glucose (2 hours post OGTT) and glucose area-under-the-curve compared to baseline values.

**CT of the abdomen:** A non-contrast CT of the abdomen to quantify visceral adiposity will be obtained at the baseline visit and again at week 40. This imaging technique is among the most reliable for measuring visceral fat (32). Scans will be

obtained at 5 levels: spleen/liver, L3-4 lumbar disc, L4-5 lumbar disc, lower edge of pubic symphysis, and upper thigh (with reference to edge of lower symphysis). The area of the visceral and subcutaneous abdominal fat compartments at the

5 levels will be measured and recorded in centimeters squared. Abdominal visceral volume will then be calculated (in liters) using the visceral tissue areas of the 5 scans and the measured distances between them. The same CT scanner will be used at the start and completion of the study, and the same radiologist at VA Palo Alto will analyze all scans.

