**Insulin Sensitivity Test (IST):** Endogenous insulin sensitivity will be measured using a 3-hr insulin sensitivity test (33,34). This test will be performed at baseline and again at week 43 (which follows a 3-week washout period for study medications). An intravenous catheter will be placed into each antecubital vein. One catheter will be used for blood draws for glucose measurements and the catheter in the contralateral arm will be used for infusion of octreotide, insulin and 20% dextrose. The 3 infused substances will be administered simultaneously. Octreotide acetate will be used to suppress endogenous secretion of insulin and will be infused at 0.27 µg/m2 per minute. Insulin will be infused at 32 mU/m2·min and glucose will be infused at 267 mg/m2 per minute. Serum glucose will be measured every 30 minutes for the first 150 minutes and then every 10 minutes during the last half hour of the test. The last 4 serum glucose measurements will averaged and recorded in mg/dl and will constitute the subject’s steady state plasma glucose (or SSPG). The SSPG provides a direct measure of insulin-mediated glucose uptake and will be used to describe each subject’s insulin sensitivity (33,34).

**Anthropometrics:** BMI, waist circumference and WHR will be measured at baseline and at weeks 8, 16, 32 and 40.

**IGF-1 levels:** Serum insulin like growth factor 1, or IGF 1, is a marker of GH status in the body. IGF 1 levels will be drawn at baseline and again at weeks 8, 16 and 32 and will be used along with clinical symptoms to assess rhGH dose adequacy. IGF 1 values greater than 2 standard deviations above the adult reference mean will result in a 50% rhGH dose reduction.

**Liver function tests, fasting glucose, hemoglobin (Hgb) A1C:** LFTs will be obtained at baseline and again at weeks 8, 16, 24, 32 and 40. Fasting glucose levels will be measured at baseline and at weeks 4, 8, 12, 16, 20, 24, 32 and 40. A HgbA1C will be used to measure each subject’s long-term glucose control and will be obtained at baseline and at weeks 8, 16 and 40.

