TZDs versus diet plus exercise: An alternative approach that might obviate the need for insulin sensitizer therapy is diet and exercise. However, this approach will not be used in this study for two reasons. First, many

viscerally obese, IGT adults have already tried diet and exercise and failed. Secondly, previous studies have shown that diet and exercise cannot overcome the transient insulin resistance and hyperinsulinemia associated with rhGH (44,45).

E. **METHODS OF DATA ANALYSIS**

   Data will be analyzed using StatView software for Microsoft Windows (SAS Institute Inc., Cary, NC). All data will be expressed as the mean +/- SE. A Student’s *t* test will be used to compare baseline values of the subject groups. For measurements pertaining to visceral fat, insulin sensitivity and glucose metabolism, ANOVAs for repeated measures will be used to analyze differences between data obtained at all time points. Area under the curve (AUC) for glucose data will be determined using the trapezoid method. In addition, results will be considered significant at *P* < 0.05.

F. **SIGNIFICANCE**

A. **Prevention of type 2 diabetes** **in viscerally obese adults with IGT**

The growing health care burden of type 2 diabetes mellitus in the U.S. demands that newer, more effective diabetes prevention strategies be implemented. One way to achieve diabetes prevention is to target adults who are at greatest risk for developing diabetes, such as viscerally obese adults with IGT.

Recent studies like the Diabetes Prevention Program (DPP) Trial indicate that, in individuals with IGT, interventions that result in visceral fat reduction also significantly reduce the risk of developing overt diabetes. Unfortunately, in non-experimental settings, many obese individuals have had little success in achieving visceral fat reduction with current weight loss modalities such as diet, exercise or anorexogenic drugs. This lack of success is often related to noncompliance and recidivism with diet and exercise and with limited overall benefit, intolerable side effects and/or addictive potential with anorexogenic medications. Furthermore, the potent weight-reducing effects of bariatric surgery are often eclipsed by severe gastrointestinal complications postoperatively and, in rare circumstances, an increase in mortality.

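### Specific aim 2 promises short-term answers on insulin resistance and postprandial glucose, but neither is measured between baseline and week 43, and only one fasting glucose falls in the 6-week window

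*Protocol*

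**What the plan says.** Hypothesis 2 (Protocol, section B) predicts that the combination will show less transient "worsening in glycemic control during the first 6 weeks of treatment compared with subjects who receive rhGH alone". Its specific aim opens with a general comparison of short-term glucose metabolism between a TZD plus rhGH and rhGH alone. It then adds two particular questions: whether a TZD "can effectively counteract the expected transient rise in insulin resistance associated with rhGH", and whether it will "help to maintain better short-term postprandial glucose control compared with rhGH alone".

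The Abstract names the short-term measure: "Short-term glucose metabolism will be monitored using fasting glucose levels". Study Endpoints gives the timing: "Fasting glucose levels will be measured at baseline and at weeks 4, 8, 12, 16, 20, 24, 32 and 40". For postprandial glucose, the same section says that "a 75 gram OGTT will be repeated at week 43, approximately 3 weeks after discontinuation of all study medications"; the only other OGTT is the one before treatment. The insulin sensitivity test (IST) is done at baseline and week 43, also after the washout.

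Experimental Design starts the treatment period at week 0, with pioglitazone or oral placebo. Study drugs starts rhGH at week 5.

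**The concern.** A trial can determine an effect on insulin resistance or postprandial glucose in a given period only if something that reflects it is measured in that period. Here the two particular questions in the aim concern the first weeks of rhGH, while the two tests that would answer them come before treatment and long after that period. A later statistical analysis plan cannot repair this, because it cannot analyse measurements that were never taken.

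What remains is fasting glucose, and the Background gives a reason for caution in using it as a stand-in for resistance. Despite the action of GH against insulin, "euglycemia is usually maintained because the pancreatic beta-cell increases insulin output in order to overcome tissue insulin resistance". If the aim stays as worded, a fasting-glucose result is likely to be reported as evidence on insulin resistance or postprandial control that it does not contain. Hypothesis 2 is one of only two hypotheses in the trial.

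**Working it through.** The plan gives no sample size, power or alpha figure for Hypothesis 2, so there is no figure to reproduce. The check counts scheduled assessments inside the window.

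**Inputs (Protocol)**
- Window length: 6 weeks (section B).
- Start of study treatment: week 0 (Experimental Design). Start of rhGH: week 5 (Study drugs).
- Fasting glucose: baseline and weeks 4, 8, 12, 16, 20, 24, 32, 40, so 8 post-baseline values (Study Endpoints).
- HgbA1C: baseline and weeks 8, 16, 40 (Study Endpoints).
- OGTT: screening and week 43. IST: baseline and week 43 (Screening Tests; Study Endpoints). The columns of the Tentative Sequence table are broken in the text, but it shows one OGTT mark and two IST marks, so it adds no early test.

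**Step 1: count visits after the start and up to the end of the window.** The start of rhGH can be read as 4 elapsed weeks (the beginning of week 5), giving 4 + 6 = 10, or as the number 5, giving 5 + 6 = 11.

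| Window | Fasting glucose | HgbA1C | OGTT | IST |
|---|---|---|---|---|
| From week 0: weeks 0 to 6 | week 4 (before rhGH) | none | none | none |
| From rhGH start: elapsed weeks 4 to 10 | week 8 | week 8 | none | none |
| From rhGH start: weeks 5 to 11 | week 8 | week 8 | none | none |

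On every reading there is one fasting glucose (1 of 8 post-baseline values), no OGTT and no IST. Week 12 is outside each time. HgbA1C at week 8 does not fill the gap: the protocol presents it as a measure of long-term control, and it captures neither insulin resistance nor the response to a glucose load.

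**Step 2: match each claim to a measurement in the window.**
- Glycemic control (Hypothesis 2): fasting glucose at week 8, with week 4 as the last value before rhGH. Answerable in part, if the window starts with rhGH.
- Counteracting the rise in insulin resistance (aim): nothing measured.
- Short-term postprandial glucose (aim): nothing measured.

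**Step 3: ask whether fasting glucose can stand in for resistance.** The Background describes an earlier rhGH trial in abdominally obese men in which insulin sensitivity fell over the first 6 weeks while glucose levels overall did not change. Suppose fasting glucose at week 8 is the same in group 2 (rhGH alone) and group 4 (pioglitazone plus rhGH). That fits equal resistance in both groups, fully compensated. It also fits less resistance in group 4, with compensation hiding the excess in group 2. Glucose alone cannot separate the two.

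**Step 4: cost of a factorial contrast, should one be wanted.** Take 15 per group and a common variance σ² for the outcome. Group 4 minus group 2 has variance 2σ²/15. The contrast (group 4 − group 3) − (group 2 − group 1) has variance 4σ²/15. The ratio of standard errors is √(4/2) = √2 ≈ 1.41, so the factorial contrast is about 41% less precise.

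**The case against.** The strongest reply is that the hypothesis and the lead sentence of the aim do have a measurement. Hypothesis 2 mentions only glycemic control, the Abstract assigns short-term glucose metabolism to fasting glucose, week 8 lies within 6 weeks of starting rhGH, and week 4 gives a value just before it. This stands, and it confines the problem to the second sentence of the aim.

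The week-0 reading of the window is also the weaker one. The Abstract and section F both tie the 6 weeks to rhGH. But Experimental Design starts the treatment period at week 0 and Hypothesis 2 speaks only of treatment, so the starting point needs stating.

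Nor is fasting glucose useless. The Background says IGT develops when the pancreas cannot make up for resistance, and section H says glucose may rise transiently under rhGH. A difference at week 8 would therefore be informative about glycemia. The weakness lies in what a null result would mean for resistance.

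A reader might infer three stronger points that the document does not support.
- *The comparison uses the wrong reference point.* No section fixes change from baseline for Hypothesis 2.
- *The analysis dilutes the one relevant visit.* Section E says "ANOVAs for repeated measures will be used to analyze differences between data obtained at all time points", but the contrast, visit and covariates within that model are commonly settled in a statistical analysis plan, which is not at hand.
- *Pioglitazone's own glucose lowering would be misread as protection, so a factorial contrast is required.* The hypothesis compares the combination with rhGH alone and claims no interaction, and pioglitazone is deliberately started 4 weeks earlier. Offsetting an rhGH effect through pioglitazone's own action is a fair meaning of counteracting it.

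**Conclusion.** The point holds for the specific aim. Two of its stated questions, short-term insulin resistance and short-term postprandial glucose, have no observations in the window and cannot be answered. The remaining measure supplies one value in the window, and on the week-0 reading that value precedes rhGH. By the protocol's own account, a null fasting-glucose result would not inform the resistance question.

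It would go too far to conclude that Hypothesis 2 as a whole cannot be tested. Counted from the start of rhGH, the week-8 fasting glucose, read against week 4, gives a thin but legitimate test of glycemic control.

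The conclusion rests on the schedule as written and needs no assumed effect size. This should be fixed but is not critical: the study is powered on visceral fat and on insulin sensitivity, and neither depends on this aim.

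**What to change.** 1. State in Hypothesis 2 that the 6 weeks run from the start of rhGH.
2. Limit specific aim 2 to fasting glucose, comparing group 4 with group 2 at week 8 and using the week-4 value, the last before rhGH, as reference or covariate.
3. Delete the short-term postprandial claim. Keeping it would require a postprandial test inside the window, which means an added procedure for every subject.
4. Either delete the insulin-resistance claim or support it by assaying fasting insulin on the fasting blood already drawn at weeks 4 and 8. Read with glucose, this would show the compensation the Background describes, though less directly than the IST.
5. Treat the factorial contrast as optional. If it is added, say how it ranks against the comparison in item 2 and acknowledge its standard error, about 1.4 times larger.

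The cost is a few sentences, a narrower claim and, if insulin is assayed, a small laboratory expense. No visit, blood draw or treatment changes under items 1, 2, 4 and 5, or under item 3 if the claim is deleted.
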